#### Data collection methods

2.3.4

##### Data collection

2.3.4.1

The data collection method will be consistent with that of our pilot study.

##### Data management

2.3.4.2

The entire research team will be trained in data collection and storage. As our data will be obtained through electronic surveys, we will ensure the quality of questionnaire submission by limiting the occurrence of missing values and outliers in the electronic questionnaire. After de-tagging, all uploaded data will be stored in a dedicated encrypted database, and only the lead researcher will have access to the complete data. The data analyst only will have access, and the other researchers will not have access to the data unless specifically authorised by the lead researcher. All data management processes will comply with the privacy protection principles and the Data Security Law of the People’s Republic of China.

#### Quality control

2.3.5

Before the formal investigation, we will train the community and street staff to unify the standards and investigation methods to ensure that the investigation data are objective and accurate.To ensure that the survey results are true and accurate for items that older people do not understand during the filling process, we will use a unified language to explain them.The questionnaire star will be set up to ensure that each option is filled in to ensure the completeness of the content and efficiency of the recovery.The obtained data will be double-checked; if there is any difference, the data will be checked with the original data and corrected to ensure accuracy.

#### Data preprocessing

2.3.6

We will sort the collected questionnaires and upload the data. We will use Excel to establish the database and SPSS (version 29) for preliminary data analysis. Statistical significance is set at *p* < 0.05. We will use descriptive statistics for our general data, such as frequency and ratio. In addition, we will conduct data cleaning, outlier processing, data conversion, and other preprocessing of the data.

### Phase 4 LCA

2.4

In this phase, we will conduct LCA. By analysing CBRN-Q filled out by the respondents, we will identify exactly which CBR requirement types they have (including body function rehabilitation, mental function rehabilitation, individual activities, social participation, information needs, and environmental rehabilitation), and according to these types of demand at the group level is divided into several different categories, the basic framework is shown in Figure 3 to understand further the diversity of the rehabilitation needs of older adults in the community-based and to classify them accurately. We will use MPlus software (version 7.0) for LCA with the collected data through parameterisation, estimation, evaluation, classification, and interpretation of the results. Simultaneously, we will verify the factors that influence the needs of older adults by adding covariates.

**Figure 3 fig3:**
[figure not shown]
Concept map of a latent class of rehabilitation needs of older adults.

#### Model parameterisation

2.4.1

LCA contains manifest variables, latent variables, latent-class probabilities, and conditional probabilities. The latent class probabilities represent the probability that an observation object randomly selected from the sample belongs to latent class *t*, and the sum of all latent class probabilities is 1. The conditional probability represents the probability that a sample is randomly selected from the latent class and answered using the manifest variable. The greater the conditional probability value, the greater the influence of the latent variable on the external variable (52). In this step, we will convert the categorical variables processed in the cross-sectional survey into parameters required for model construction, which is the basis of LCA.

#### Parameter estimation

2.4.2

After parameterisation, we will use the maximum likelihood method for model estimation. Currently, the commonly used methods are expectation maximisation (EM) and the Newton–Raphson method. Since EM is not affected by initial value selection, it is now widely utilised (53). In our study, we will also use this method, starting from an initial model with only one class for all samples and using a step-by-step iterative method to gradually increase the number of classes until the optimal model is found.

#### Evaluation and classification

2.4.3

Evaluation indicators commonly used in LCA models will be used to evaluate our models, such as the Akaike Information Criterion, Bayesian Information Criterion (BIC), and sample-size-adjusted box BIC (aBIC). It is believed that the accuracy of using BIC for evaluation is higher when the sample size is large; therefore, we have chosen BIC for the evaluation of this index (52). The smaller the value, the better the fitting degree of the model. Classification accuracy will be evaluated using entropy, which ranges from 0 to 1; the closer the value is to 1, the more accurate the classification (54). Finally, the Lo–Mendel–Rubin and bootstrap-based likelihood ratio tests will be used to evaluate the fitting differences of the LCA models. Statistical significance is set at *p* < 0.05.

#### Interpretation of the results

2.4.4

Once the LCA model is determined, each participant will be assigned to one of the need pattern categories with the highest probability. Through LCA, we will answer our study questions (i) and (ii) and provide a scientific explanation to identify the multiplicity and latent class of rehabilitation needs of older adults in the community and the distribution proportion of each category.

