#### Sampling

2.3.3

LCA model building requires numerous parameters, resulting in a sample size that depends on the necessary model analysis. Therefore, standard sample size calculations cannot comply with LCA requirements. For LCA, some researchers have suggested a minimum sample size of 500 (49), whereas others recommend a minimum sample size ranging from 300 to 1,000 (50, 51); therefore, we plan to recruit at least 4,000 participants. The sample size will satisfy the analytical requirements.

A probability-proportionate-to-size (PPS) sampling method will be used to select participants from Guizhou Province. PPS sampling requires the number of clusters to be not less than 30. In this study, we will assume the selection of 50 groups, with 4,000 people categorised into 50 groups, each containing 80 participants. These 50 groups will be drawn from six county-level cities and three autonomous prefectures. The number of clusters (*n*) in each of six county-level cities and three autonomous prefectures will be calculated as follows: ① The population aged ≥60 years in Guizhou Province (*N*) divided by 50 and ② The number of clusters (*n*) will be equal to the number of integer multiples of n/50 in the corresponding city cumulative population interval. Then, *n* natural villages/streets in the corresponding prefecture-level cities will be randomly selected as *n* clusters relative to the cities. Detailed information on each prefecture-level city cluster is presented in Table 2.

**Table 2 tab2:** Clusters in six county-level cities and three autonomous prefectures.

Township	Population	Accumulative population	*n* of clusters
1.Guiyang	795,475	795,475	7
2.Zunyi	1,126,525	1,922,000	9
3.Liupanshui	409,888	2,331,888	3
4.Anshun	392,951	2,724,839	3
5.Bijie	954,763	3,679,602	8
6.Tongren	579,146	4,258,748	5
7.Qiandongnan	642,509	4,901,257	5
8.Qiannan	585,724	5,486,981	5
9.Qianxinan	443,626	5,930,607	4
Total	*N*	5,930,607	50

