#### Exploration of influencing factors

2.4.5

Differences in the characteristics of respondents in different categories of demand patterns will be analysed using the Kruskal–Wallis rank tests (for ordinal measurements), one-way analysis of variance (for interval measurements), or chi-square tests (for nominal measurements). We will also perform a polynomial regression analysis to determine the factors that influenced the categories of needs of older adults, primarily by dividing the potential classes of rehabilitation of older adults obtained by LCA into dependent variables. According to the theoretical framework, relevant covariates will be included to analyse the influencing factors of the older adults’ CBR needs. The influencing factors in the theoretical framework will determine the dimensions of the collection of covariates. The covariates and their allocations are listed in Table 3.

**Table 3 tab3:** Covariates included in the analysis of influencing factors of older adults’ community-based rehabilitation needs.

Covariate	Definition/Measuring tools	Variable type	Units/categories

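### Need classes are assigned by highest probability and then tested and regressed with no allowance for misclassification, which usually dilutes the associations for research question (iii)

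*Protocol article*

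**What the plan says.** Section 2.4.4 fixes the assignment rule: once the model is determined, "each participant will be assigned to one of the need pattern categories with the highest probability".

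Section 2.4.5 uses the resulting categories in two ways. First, group comparisons: "Differences in the characteristics of respondents in different categories of demand patterns will be analysed using the Kruskal–Wallis rank tests", with analysis of variance or chi-square tests for other variable types. Second, a regression: "We will also perform a polynomial regression analysis to determine the factors that influenced the categories of needs of older adults", carried out by "dividing the potential classes of rehabilitation of older adults obtained by LCA into dependent variables", with the Table 3 covariates as predictors.

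Two other places bear on this. Section 2.4 says that "we will verify the factors that influence the needs of older adults by adding covariates", without naming a model. Section 2.4.3 says "Classification accuracy will be evaluated using entropy, which ranges from 0 to 1"; it sets no minimum and does not carry the result into section 2.4.5.

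Nowhere does the article mention posterior weighting, a corrected three-step method or a one-step latent class regression.

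**The concern.** A modal class is an estimate. Some participants are put in the wrong class, and an analysis that treats the label as known mixes the true classes within each assigned class. Covariate differences between classes then usually look smaller than they are. A large sample does not help, because it narrows the interval around a diluted value.

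Research question (iii) in section 1.3 asks which factors are associated with the needs, and section 2.4.5 is the only place where a procedure for answering it is described. Real determinants of need could be understated or missed, and the Discussion intends the results to guide targeted services and investment.

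Two wording problems add to this. The regression is called polynomial although its outcome is a set of nominal classes. And adding covariates to the latent class model (section 2.4) is a different analysis from regressing an assigned class on covariates (section 2.4.5).

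**Working it through.** **Inputs from the article.** Section 2.3.3 plans "4,000 people categorised into 50 groups, each containing 80 participants": 50 × 80 = 4,000, which reproduces the stated size. Section 2.4 lists six need types, and section 2.1.3 wants data that convert to binary variables.

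**Assumptions, not in the article.** Three classes: low on all six items, high on the first three, high on all six. An item is endorsed with probability h where high and 1 − h where low. One binary covariate x has 50% prevalence and true log odds ratios, against the low class, of ln 2 = 0.693 and 2 ln 2 = 1.386. Class shares are 0.500 / 0.300 / 0.200 at x = 0 and, from weights 1 : 1.2 : 1.6, 0.263 / 0.316 / 0.421 at x = 1.

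**Mechanism.** With W the assigned and C the true class,

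P(W = s | x) = Σ over t of P(C = t | x) × P(W = s | C = t).

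At h = 0.80, enumerating the 64 response patterns gives these rows of P(W | C): (0.893, 0.093, 0.014), (0.103, 0.803, 0.094), (0.055, 0.093, 0.852).

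- x = 0, low class: 0.500 × 0.893 + 0.300 × 0.103 + 0.200 × 0.055 = 0.4884. The other two are 0.3060 and 0.2056.
- x = 1, by the same sum: 0.2907, 0.3172, 0.3921.
- Second class: ln[(0.3172/0.2907) / (0.3060/0.4884)] = 0.555, against 0.693.
- Third class: ln[(0.3921/0.2907) / (0.2056/0.4884)] = 1.16, against 1.386.

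**Simulation at n = 4,000.** There were 500 replicates per row. The latent class model was fitted by EM started at the true values, with no cluster effect. The corrected estimate inverts the estimated misclassification matrix. Pairs are for the two contrasts.

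| h | Entropy | Misclassified | Modal-class log OR | Shrinkage | 95% coverage | Corrected log OR |
|---|---|---|---|---|---|---|
| 0.95 | 0.96 | 1.0% | 0.690 / 1.380 | 0–1% | 96% / 94% | 0.696 / 1.391 |
| 0.90 | 0.88 | 3.9% | 0.668 / 1.336 | 4% | 94% / 91% | 0.697 / 1.386 |
| 0.85 | 0.77 | 8.6% | 0.624 / 1.267 | 9–10% | 85% / 68% | 0.695 / 1.387 |
| 0.80 | 0.63 | 14.8% | 0.566 / 1.166 | 16–18% | 62% / 23% | 0.697 / 1.392 |
| 0.75 | 0.49 | 22.2% | 0.486 / 1.018 | 27–30% | 23% / 1% | 0.687 / 1.385 |

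Shrinkage is 1 − estimate/truth; at h = 0.80, 1 − 0.566/0.693 = 18% and 1 − 1.166/1.386 = 16%. As odds ratios, a true 2 becomes exp(0.566) = 1.76 at entropy 0.63 and exp(0.486) = 1.63 at 0.49.

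**Bias or standard error?** The naive standard error is about 0.08 in every row. It roughly matches the spread of the diluted estimate itself (0.075 to 0.083), so the lost coverage comes mainly from bias. The spread of the corrected estimate is larger: 0.092 / 0.092 at entropy 0.77, 0.109 / 0.101 at 0.63 and 0.130 / 0.123 at 0.49. With the bias removed but the naive standard error kept, coverage would be 91% / 91%, 84% / 87% and 78% / 80% in those rows. Omitted classification uncertainty is thus a second, smaller effect.

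**Sensitivity to the indicators.** Section 2.2.1 expects 40–45 items. In a smaller check (60 replicates, 3 classes, n = 4,000, same starting rule) with 42 items, h = 0.75 gave entropy 0.98 and under 1% shrinkage. Weaker items, at 0.65 / 0.35, gave entropy 0.75 and about 9–12%.

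**The case against.** The strongest reply is that a condensed article leaves the estimator to a fuller plan. Section 2.4.5 makes the classes obtained by the latent class analysis the outcome without saying in so many words that the modal label is used, and section 2.4 speaks of adding covariates. This has some weight: a reader might infer that the modal-class regression is the sole analysis for question (iii), and section 2.4 leaves room for another. But the article does state the assignment rule, the tests, the regression and the covariates, and the sentence in section 2.4 names no model that would repair them.

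A reader might also take the word polynomial to mean powers of a predictor for a continuous outcome. The outcome is a category of need, so multinomial is evidently meant. It is a slip that needs one word changed.

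It is further fair to say that the size rests on assumed separation and an assumed indicator set, that entropy will be reported so poor classification would be visible, and that finding the classes for questions (i) and (ii) does not depend on this regression. All of that stands, and it limits the severity. It does not remove the point, because nothing in the plan says what follows if entropy turns out low.

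**Conclusion.** The point holds as a should-fix. As written, the plan classifies and then analyses with no stated allowance for classification error, and this usually attenuates the associations for question (iii). Under the assumed three-class, six-indicator setting the loss is negligible at entropy 0.96, about a tenth at 0.77 and more than a quarter at 0.49. The actual size cannot be known before data, and with 40–45 reasonably discriminating items it could be close to nil.

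Two stronger readings are not supported. One is that the standard errors are simply wrong: they fit the diluted estimate, and are too small only as a measure of uncertainty about the true-class association. The other is that every odds ratio moves toward 1: with several classes, single contrasts can move otherwise.

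Standard errors that respect the clustered sample are a separate matter.

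**What to change.** In section 2.4.5, replace the polynomial regression on the assigned class with multinomial logistic regression of latent class on the Table 3 covariates. Use either a bias-adjusted three-step method (for example R3STEP in Mplus) or a one-step latent class regression, and say which is primary. The article states "We will use MPlus software (version 7.0) for LCA with the collected data", so confirm that the chosen option is available in that version. Reword section 2.4 so that adding covariates refers to the same analysis.

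In section 2.4.4, report class proportions from the model rather than from counts of assigned participants. Keep modal class, and the Kruskal–Wallis, analysis-of-variance and chi-square comparisons across it, for description only.

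The cost is analysis wording and wider intervals; no new data are needed. Dividing the corrected spread by the naive standard error gives the widening under the same assumptions:

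- Entropy 0.88: 0.082/0.078 and 0.081/0.081, so 0–5%.
- Entropy 0.77: 0.092/0.078 and 0.092/0.081, so 14–18%.
- Entropy 0.63: 0.109/0.078 and 0.101/0.080, so 26–40%.
- Entropy 0.49: 0.130/0.077 and 0.123/0.079, so 56–69%.

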### Study questions

1.3

This study hypothesises that older adults have physiological, psychological, and social participation and environmental and information needs in CBR. Since older adults have multiple needs at the same time, there may be several fixed combinations of these needs in the older adults population (e.g., “Physiological-psychological” combination, “socially-participation-environment” combination). Each older adults person will fall into one of these categories, and contextual characteristics, individual characteristics, health behaviours, and health outcomes influence these combinations.

We aim to address the following three research questions: (i) When older adults individuals have multiple rehabilitation needs, is it more likely that these needs will be combined in a specific manner rather than randomly? (ii) Do older adults with similar characteristics have similar needs? (iii) What key factors are associated with the needs of older adults with multiple CBR needs?

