#### The Delphi method

2.1.3

The Delphi method is intended to score and guide the importance and feasibility of constructing an older adult’s CBRN-Q (37).

The researchers will first establish an expert group that includes rehabilitation medicine doctors, geriatric medicine experts, geriatric nurses, and rehabilitation nursing experts. Members of this team must have >10 years of clinical experience and intermediate or higher professional titles. More than 15 experts will be involved in this stage (38).

The survey will include an expert letter questionnaire conducted via e-mail correspondence, a questionnaire that includes the study background, an expert general situation questionnaire, and the main body of the questionnaire. The expert will evaluate the importance (rated on a Likert scale from very important, 5, to unimportant, 1) and feasibility (very low to too much) of each item in the CBR needs questionnaire for older adults. The researchers will summarise, screen, and modify the opinions put forward by experts on older adults’ CBR needs questionnaire items, request the experts for consultation again, and repeat the process until the experts stop contributing their opinions (39). Entries that meet the following criteria will be retained: the mean value of the importance assignment X > 3.5 and the coefficient of variation (CV) < 0.25 (40).

Finally, the research group will discuss expert opinions and suggestions to further improve the older adults’ CBR needs questionnaire. Simultaneously, since the core of the study is the model construction and analysis based on LCA, there should be a clear boundary value for both the scale and items used so that the data can be easily converted into binary variables for analysis.

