#### Study sample and sample size

2.2.1

Using purposive sampling, we will conduct a questionnaire survey on older adults in Zunyi, Guizhou Province. The sample size for questionnaire verification should be 10 times the number of questionnaire items (41). Because the questionnaire we developed is estimated to have 40–45 items, we will need at least 450 participants. Considering a 10% loss to follow-up rate, we determine that the sample size of the pre-trial is 500 participants.

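### Finding several latent classes shows that needs are not combined at random, but not that they form distinct combinations; question (i) needs a one-factor comparator, and question (ii) belongs to section 2.4.5

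*Protocol article*

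**What the plan says.** Study questions (1.3) asks, as question (i), "is it more likely that these needs will be combined in a specific manner rather than randomly", and as question (ii), "Do older adults with similar characteristics have similar needs". The hypothesis behind (i) is that "there may be several fixed combinations of these needs in the older adults population", with a physiological-psychological combination given as an example.

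Interpretation of the results (2.4.4) allocates both questions to one method: "Through LCA, we will answer our study questions (i) and (ii".

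The indicators are needs only. Phase 4 LCA (2.4) says "By analysing CBRN-Q filled out by the respondents, we will identify exactly which CBR requirement types they have" and lists six types. The Delphi section (2.1.3) asks for cut-offs "so that the data can be easily converted into binary variables for analysis", and the pilot section (2.2.1) says "the questionnaire we developed is estimated to have 40–45 items".

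The number of classes is set in 2.4.2 and 2.4.3. The analysis starts from one class, adds classes, and judges them by BIC, with entropy, the Lo-Mendell-Rubin test and the bootstrap likelihood ratio test alongside. Respondent characteristics enter in 2.4.5 and Table 3, where they are compared across classes and used as predictors of class.

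Model parameterisation (2.4.1) also states: "The greater the conditional probability value, the greater the influence of the latent variable on the external variable".

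**The concern.** Question (i) has two halves. One is whether needs are combined at random. The other is whether they combine in particular ways, which the hypothesis spells out as distinct bundles. The one-class model stands for the first possibility, because it means independent needs. No model in the plan stands for the obvious rival to distinct bundles, namely that frailer people need more of everything. That rival is plausible here: the Background already says that needs tend to occur together, and Table 3 lists self-care ability and frailty as influences.

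The stakes are practical. The study is meant to support personalised services by subtype. Distinct bundles would argue for different service packages, while a severity scale would argue for graded amounts of the same services. If low, medium and high classes were reported as need combinations, the main conclusion would point the wrong way.

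For question (ii), a model that sees only needs cannot say whether people with similar characteristics have similar needs.

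**Working it through.** **Inputs from the protocol.** Main sample: 50 clusters × 80 = 4,000, which reproduces the figure in 2.3.3. Indicators: binary; six need types (2.4), or 40 to 45 items (2.2.1). Selection: lowest BIC, starting from one class (2.4.2, 2.4.3).

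**Assumptions, not in the protocol.** Participants are independent, so clustering is ignored. Under a gradient, logit P(need j) = a·θ + b_j, with θ standard normal and no classes. Slopes a run from 0.5 to 3. The b_j are set from base prevalences of 0.55, 0.35, 0.30, 0.40, 0.45 and 0.50 for six needs, and from 0.20 to 0.60 for 40 items. On the underlying logistic scale the correlation between two needs is a²/(a² + π²/3): 0.25/3.54 = 0.07 at slope 0.5 and 9/12.29 = 0.73 at slope 3. The range therefore covers weak to strong gradients.

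**Formulas.** BIC = −2 log L + p ln(4,000), with ln(4,000) = 8.294. A K-class model of six needs has p = (K − 1) + 6K, that is 6, 13 and 20 parameters for one, two and three classes. The one-factor model has p = 12. Going from one class to two costs 7 × 8.294 = 58.1, so BIC prefers two classes once the likelihood ratio statistic exceeds about 58.

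**Six needs, n = 4,000, 30 data sets per row, 1 to 5 classes fitted.**

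| Data generated under | Classes chosen by BIC | One-factor model has lower BIC than chosen LCA | Classes ordered on every need |
|---|---|---|---|
| Independent needs | 1 in 30 | 0 of 30 | one class only |
| Gradient, slope 0.5 | 2 in 30 | 30 of 30 | 30 of 30 |
| Gradient, slope 1 | 2 in 26, 3 in 4 | 30 of 30 | 30 of 30 |
| Gradient, slope 1.5 | 3 in 30 | 30 of 30 | 30 of 30 |
| Gradient, slope 2 | 3 in 30 | 30 of 30 | 30 of 30 |
| Gradient, slope 3 | 3 in 30 | 30 of 30 | 30 of 30 |
| Three truly crossed classes | 3 in 30 | 0 of 30 | 0 of 30 |

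Over the 5 × 30 = 150 gradient data sets, one class was never chosen. An example at slope 1.5 has class shares of 33%, 47% and 20%, with need probabilities of 0.04–0.18, 0.34–0.63 and 0.73–0.91. These are low, medium and high need. Crossed classes gave three classes, the same number as a gradient of slope 1.5 or more, so the class count does not separate the two explanations. The one-factor comparison did so in every gradient and crossed-class data set.

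**Forty items, n = 4,000, three gradient data sets per slope.** BIC chose 4 classes at slope 1, 5 at slope 1.5, and 5 (one data set) or 6 (two data sets) at slope 2, where 6 was the most fitted. All nine were ordered, and the one-factor model had the lower BIC in all nine.

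**Question (ii).** Sections 2.4.1 to 2.4.4 describe a model of need indicators. People in one class resemble each other in needs because that is how classes are formed. Characteristics meet the classes only in 2.4.5.

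**The sentence in 2.4.1.** In the slope 1.5 example the first need has conditional probabilities of 0.18, 0.63 and 0.91, a spread of 0.91 − 0.18 = 0.73. A need endorsed at 0.9 in every class has an equally high conditional probability and a spread of 0, so it says nothing about class. Size alone does not measure dependence on class.

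**The case against.** A reader might infer that the plan will answer question (i) with yes almost whatever the truth. The protocol does not support that. The null named in 1.3 is random combination, the one-class model is exactly that, and BIC kept one class in 30 of 30 independent data sets. The plan can answer no to the question of randomness.

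A reader might also infer that a severity scale could not be told apart from real combinations. That too goes too far. The gradient classes were ordered on every need, and an analyst who reads the class profiles would see it. Nothing in the protocol says that ordered classes would be reported as combinations. What remains is that the named criteria contain no rival model and no rule for the case of ordered profiles.

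On question (ii), calling the plan circular, or saying that it ignores characteristics, is not supported. Section 2.4.5 sits inside Phase 4, and it compares characteristics across classes and regresses class on the Table 3 covariates. That analysis bears on (ii). Reading 2.4.4 as meaning all of Phase 4 is fair, which makes this a matter of allocation.

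The sentence in 2.4.1 is a loose gloss. No later step uses it to select or judge items, so it is a wording error and not a faulty decision rule.

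The simulations depend on assumed slopes and prevalences, and they apply BIC only.

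**Conclusion.** The point holds in a limited form. The planned rule can show that needs do not combine at random. By itself it cannot support the hypothesised fixed combinations, because a single gradient gave 2 or 3 ordered classes in 150 of 150 six-need data sets and 4 to 6 in nine 40-item data sets. A one-factor comparator favoured the gradient in all 159 of these (150 + 9) and the latent class model in 30 of 30 crossed-class data sets.

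This rests on a normally distributed severity factor, logit slopes of 0.5 to 3 (1 to 2 for 40 items), the stated prevalences, independent participants, and BIC as the selector. The Lo-Mendell-Rubin and bootstrap tests were not simulated. How strong a gradient exists in the target population is unknown.

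Question (ii) is credited to the wrong step but can be answered from analyses already planned. The 2.4.1 sentence is wrong as a statement but has no consequence elsewhere in the plan.

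**What to change.** 1. In 2.4.3, add a one-factor (item response) model on the same binary indicators, fitted by maximum likelihood so that its BIC is comparable, and compare it with the chosen latent class model.
2. In 2.4.4, state that specific need combinations will be claimed only if the latent class model is preferred and the class profiles cross, and say in advance what counts as crossing. Otherwise report a severity gradient.
3. In 2.4.4, let the latent class analysis and this comparison answer question (i), and assign question (ii) to the analyses in 2.4.5 that relate characteristics to class.
4. In 2.4.1, say that differences in conditional probability between classes, not its size, show how strongly an item depends on class.

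The cost is one extra model and a few sentences, with no new data. The downside is that the result may be a gradient and not distinct subtypes.
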